### Variables

Reviewers in each hospital were provided with a handbook with instructions to follow in the data collection process.-Exposure variables:*Related to the patients’ personal background*: date of birth, sociodemographic variables (level of education, occupation of the patient or of the head of the household, marital status and living arrangements), height, weight, lifestyle habits, gynecological history (family history of gynecological cancer, oral contraceptives or hormonal replacement therapy, first and last menstruation date, menopausal status [pre- or postmenopausal], number of pregnancies and of births, breastfeeding [yes/no and duration]); and comorbidities (Charlson Comorbidity index) [16].*Related to the hospital*: number of beds, whether it is a teaching hospital, catchment population size, number of patients treated for breast cancer annually, and whether it has a breast cancer unit and medical or radiation oncology services.*Related to the process of care*: date of first contact with medical care (scheduled/emergency), time between the first symptoms and the first contact with medical services, time between the first medical appointment and histological diagnosis, time between diagnosis and treatment, and date of diagnosis.*Related to the pre-intervention tumor history*: mode of detection (symptomatic, screen-detected), symptoms (lump, lymph nodule, swelling or hardening of a part of breast, change in the size or shape of the breast, skin retraction, ulceration/wound, pain, secretion, inflammation, nipple retraction), date of the first symptom, clinical TNM classification (cTNM), additional diagnostic tests (ultrasound scan, magnetic resonance imaging [MRI], biopsy, computerized axial tomography [CAT], bone scan, galactography, ultrasound), histological type (infiltrating carcinoma, infiltrating ductal carcinoma, infiltrating lobular carcinoma, mucinous carcinoma, metaplastic carcinoma, intraductal carcinoma, and others) and serum marker levels (CA15-3, CA27.9, CEA, CA125).*Related to neoadjuvant treatment:* chemotherapy (regimen and whether it is completed), radiotherapy, hormone treatment, anti-HER2, and other therapies; and clinical and radiological response (assessed by MRI) categorized as no response (no changes or progression), weak partial response (if the tumor size reduced less than 50%), strong partial response (if the tumor size reduced by 50% or more), and complete response (no residual tumor) [17].*Related to surgery*: date, duration of the intervention, emergency vs scheduled, surgical technique (quadrantectomy, lumpectomy, segmentectomy, simple mastectomy, radical mastectomy, modified radical mastectomy, skin-sparing mastectomy, nipple-sparing mastectomy, contralateral prophylactic mastectomy, lymphadenectomy), time between diagnosis and intervention and/or pre-surgical adjuvant treatment, and intraoperative complications (bleeding, nerve injury, anesthetic complications, allergic reaction to the prophylactic antibiotic, others).*Related to anatomical pathology*: laterality, sentinel node biopsy (yes/no and results), histological type (intraductal, ductal, lobular, tubular, mucinous, medullary, cribriform, papillary, non-specific, others), degree of differentiation, pathological TNM (pTNM), location, size, distant metastases, vascular and nervous infiltration, number of lymph nodes analyzed and number positive, margin involvement, estrogen receptor/progesterone receptor status, Ki-67, P53, CK5/6, CK14, CK19, and HER2 expression, oncotype, and MammaPrint.*Related to admission*: setting (hospitalization vs. or ambulatory surgery), length of hospital stay in days after first intervention, in-hospital complications (seroma, wound infection, necrosis of skin flap, pneumothorax, brachial plexus pathology, and others), reintervention during admission, other medical treatments, and death.*Related to follow-up*: primary treatment: adjuvant postoperative treatment (radiotherapy, chemotherapy, hormone therapy, anti-HER2, and other therapy), date of treatments, reconstructive plastic surgery (yes/no, technique and date), other postoperative treatments (rehabilitation, psychologist/psychiatrist, others), and contact with social services; immediate complications and any reported during the follow-up period: chest wall and breast complications (seroma, post-surgery adhesions, soft tissue necrosis and recurrent skin infections), musculoskeletal (reduced arm mobility), lymphedema, neurological (paresthesias, neuropathy, cognitive dysfunction), pulmonary (pneumonitis, pulmonary fibrosis) cardiovascular morbidity (cardiomyopathy), psychological effects (anxiety), pain, other toxicities (ototoxicity, nephrotoxicity), reproductive health (premature menopause, infertility, sexual dysfunction), osteoporosis, weight gain, mycosis, and immunosuppression (agranulocytosis, lymphopenia); complications after reconstructive surgery (prosthesis infection, capsular contracture, others) and reinterventions, readmissions, death and their respective causes; and management of the disease during the follow-up period: diagnostic tests after surgery (CAT, positron emission tomography-CAT, biopsy, MRI, others), treatments (surgery, radiotherapy, chemotherapy, hormone therapy, anti-HER2, others), and number of follow-up visits per year (to the surgery/gynecology department, oncology department, rehabilitation unit, pain unit and palliative care unit).

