### Sample size calculation

We estimated the sample size based on the objective related to the creation and validation of a predictive model for which a relatively large sample size is required. The literature on prediction models indicates that a minimum of 10 outcome events are needed per predictor (relapse) [24]. Our aim is to include a limited but comprehensive list of variables (likely, not less than 10), in the multivariate regression models. Given this, we estimated that we needed at least 100 events of the dependent variable in the sample in order to ensure that the regression model converges adequately. It has been reported [25] that 7% of patients with breast cancer relapse within the first 2 years and considering this rate, we calculated the estimated sample size. Nevertheless, so far, based on 1456 patients, the relapse rate has been 4%, implying that no more than six variables should be included in the predictive models. We included all consecutive new cases until the sample size was achieved.

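### The cap of six counts variables, not estimated coefficients, so a model that obeys it can still fall below the plan's 10 events per predictor, even on all 1456 women

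*Protocol article*

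**What the plan says.** All of the sizing is in the protocol article, Sample size calculation. The rule adopted is that "a minimum of 10 outcome events are needed per predictor (relapse" being the outcome meant. The authors expected a "limited but comprehensive list of variables (likely, not less than 10" or more, and so asked for "at least 100 events of the dependent variable in the sample in order to ensure that the regression model converges adequately". With the literature figure that "7% of patients with breast cancer relapse within the first 2 years", this gave the planned sample. The observed rate turned out to be 4% of 1456 women, "implying that no more than six variables should be included in the predictive models".

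The convergence purpose is attached to the target of 100 events. The six then follows from the same rule of 10 events. Nothing in the section says that the limit counts coefficients.

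Several candidates have many categories. Under Variables, pathology records "histological type (intraductal, ductal, lobular, tubular, mucinous, medullary, cribriform, papillary, non-specific, others", which is ten categories. Table 3 reports stage in five levels, 0 to IV. The paragraph on surgical severity, under Complications, ranks nine kinds of surgery. Under Statistical analysis, the relapse model is a logistic regression built in a random 60% of the women.

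**The concern.** A variable is not a fixed unit of model complexity. A yes/no variable or a linear score needs one coefficient; a factor with k categories needs k−1. The 10-events rule protects the fit only if its denominator is the number of coefficients estimated. A cap worded in variables can be obeyed to the letter by a model with two or three times as many coefficients as the events allow.

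What is at stake is the purpose the article itself gives. A level with few or no relapses can push a coefficient towards infinity, so the fit does not converge. Too many coefficients make predicted risks too extreme in new patients. The article plans to turn these coefficients into a score for use in health records and individual decisions (Statistical analysis; Expected outcomes of the study), so instability would pass through to users.

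**Working it through.** **1. Reproduce the plan's figures.** Inputs from Sample size calculation.

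- Planned size: 100 / 0.07 = 1429, against 1456 recruited.
- Observed events: 0.04 × 1456 = 58.2. Maximum predictors: 58.2 / 10 = 5.8, rounded up to the stated six. A strict reading gives five.
- If 4% is rounded from anywhere between 3.5% and 4.5%, events lie between 51 and 66, and the limit between 5.1 and 6.6.
- Derivation set: 0.60 × 1456 = 874 women and 0.60 × 58.2 = 34.9 events, so 34.9 / 10 = 3.5, that is, three.

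**2. Coefficients that candidate variables can take.** The article does not fix these codings, so each is given as a range.

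- Stage 0–IV: 4 as a five-level factor, 3 without stage 0, 1 as a linear score.
- Pathological histology, ten categories: up to 9.
- Surgical technique, nine ranks: up to 8 as a factor, 1 as a rank.

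**3. Events per coefficient** = events / number of coefficients.

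| Model | Coefficients | All 1456 (58.2 events) | 60% set (34.9 events) | Events needed at 10 each |
|---|---|---|---|---|
| Six one-coefficient variables | 6 | 9.7 | 5.8 | 60 |
| Stage I–IV as a factor + five one-coefficient variables | 8 | 7.3 | 4.4 | 80 |
| Stage 0–IV as a factor + five one-coefficient variables | 9 | 6.5 | 3.9 | 90 |
| Stage 0–IV and histology as factors, only two variables | 13 | 4.5 | 2.7 | 130 |
| Histology as a factor, one three-level factor, four one-coefficient variables | 9 + 2 + 4 = 15 | 3.9 | 2.3 | 150 |

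Every row obeys the cap of six variables. Only the first comes close to 10 events on the whole cohort.

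**4. Sparse levels.** Adding the two columns of Table 3 gives 135, 685, 458, 138 and 29 women in stages 0 to IV (1445 staged). If no stage 0 woman relapses, that level's coefficient has no finite estimate. With relapse risk r the chance is (1 − r)^135: 51% at r = 0.5%, 26% at 1%, 7% at 2%. These risks are assumptions; the article gives no relapse rate by stage.

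**5. Overfitting.** The expected shrinkage factor S solves n = p / [(S − 1) ln(1 − R²/S)], where p is the number of coefficients and R² the Cox–Snell value. At 4% prevalence the maximum R² is 1 − (0.04^0.04 × 0.96^0.96)² = 0.285. R² is assumed to be 10% to 30% of that maximum.

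| Coefficients | S, n = 1456 | S, n = 874 |
|---|---|---|
| 6 | 0.88–0.96 | 0.81–0.93 |
| 9 | 0.82–0.94 | 0.74–0.90 |
| 15 | 0.74–0.90 | 0.63–0.84 |

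**6. Simulation, as illustration.** Logistic cohorts of 1456 were simulated with the Table 3 stage shares, assumed stage risks and effects, and no variable selection. Fits that separated or failed to converge: 0% with linear stage (6 coefficients), 25–54% with five-level stage (9), 35–60% with 15 coefficients, and 9–19% with stage 0 removed (8 to 14). Mean calibration slope among fits that converged: 0.86–0.90, 0.83–0.86 and 0.71–0.74 for 6, 9 and 15 coefficients.

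**The case against.** The best defence is that the article never says how stage, histology or surgery would enter a model. The Variables section is a data-collection list, not a model specification, and coding is commonly left to the full protocol or analysis plan, which are not shown. Some recoding is described: symptoms become one yes/no variable, three conservative techniques are grouped, and surgery is ranked by complexity, which would allow ordinal use. In situ cases are excluded from the survival analysis, though the article does not extend this to the logistic relapse model. In addition, the rule is worded per predictor and rests on a source that is not available here.

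Much of this stands, and it limits the point. A reader might infer that stage alone uses four of the six places. That holds only for an unordered five-level factor with stage 0 kept. A reader might also infer that a compliant model must overfit badly or fail to converge. The figures do not show that: with stage as the only multi-category factor, expected shrinkage on the whole cohort is 0.82–0.94. Separation comes mainly from sparse levels and turns on assumed risks. The simulation also omits the planned screening at p < 0.20, so it does not mimic the planned procedure.

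The defence does not rescue the limit itself. The cap is stated, not left open, and it is in the wrong unit. No section collapses stage or histology for modelling. That coefficients are the right unit follows from how a logistic model is estimated and does not depend on the cited source.

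**Conclusion.** The point holds as a fault in how the limit is defined. A six-variable model can meet the article's cap and still break its 10-events standard on all 1456 women: 6.5 events per coefficient at 9 coefficients and 3.9 at 15. This part is arithmetic from the article's figures and depends only on multi-category variables being entered as factors, which nothing in the article prevents.

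The consequences are conditional. Separation is possible where a level has few or no relapses, for example stage 0, or stage IV with only 29 women. Overfitting is mild to moderate at about 9 coefficients and becomes serious only with several multi-category variables and modest R². Both sizes rest on stage risks, effects and R² that the article does not give.

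A reader might also take five coefficients (5.8 rounded down) as the corrected limit in every case. It applies only to a fit on the whole cohort. In the 60% derivation set, five coefficients would have 34.9 / 5 = 7.0 events each and would still break the rule.

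**What to change.** Restate the limit as the number of estimated coefficients, counting each non-reference category and each non-linear term as one, with events counted in the data actually used for fitting. On present figures that is at most five coefficients on all 1456 women (58.2 / 10 = 5.8), or three if the 60% derivation set is kept (34.9 / 10 = 3.5). Because 4% is the rate so far, say that the number will be updated to the final relapse count.

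Add a short coding table, fixed without looking at the outcome, that gives collapsed or ordinal codings for stage, histology and surgery, and state whether in situ cases enter the relapse model.

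The cost is one sentence and one table, with no new data. The price is coarser categories and fewer variables in the model.

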### Missing data assumptions and recoding of variables

Tumor definitions:Bilateral breast cancer

Bilateral tumors with different pathological diagnoses at the time of diagnosis or up to 6 months later are described as synchronous bilateral breast cancer, while two breast tumors that occur in contralateral breasts at two different time points (more than 6 months of difference) are categorized as metachronous bilateral breast cancer. Lastly, two breast tumors with the same pathological diagnosis are considered bilateral metastatic breast cancer.2)A recurrence or recurrent breast cancer is breast cancer that has come back during follow-up after a period in which cancer had not been detected. The cancer may come back in the same or opposite breast or chest wall. We recorded local, regional and metastatic recurrence.3)A metastasis or metastatic breast cancer is defined as disease that has spread to distant sites of the body, such as the liver, lungs, bone, brain, and/or other tissues or organs [26].

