*- Patient-reported measures*

The EORTC-QLQ-C30 (version 3.0) [18, 19] is an internationally validated health-related quality of life questionnaire that is widely used in cancer research. The core questionnaire is comprised of 30 items that assess five functioning domains (physical, role, cognitive, emotional, and social); eight cancer symptom domains (fatigue, pain, nausea and vomiting, dyspnea, insomnia, appetite loss, constipation, and diarrhea); financial difficulties, and global quality of life. The scores are transformed to a 0-100 scale, with a high score implying a high level of functioning or global quality of life, while for the symptom domains, higher scores indicate greater symptom burden. In conjunction with this core questionnaire (QLQ-C30), the breast cancer specific module, EORTC-QLQ-BR23, will be used [20]. This consists of 23 items assessing disease symptoms, side effects of treatment (surgery, chemotherapy, radiotherapy and hormonal treatment), body image, sexual functioning, and future perspectives. The scoring approach is identical to that for the QLQ-C30.

The self-complete version of the EuroQol generic health-related quality of life questionnaire (EQ-5D) [21] consists of two parts: the EQ-5D-5 L descriptive system and the EQ Visual Analogue scale (EQ VAS). The descriptive system comprises five dimensions (mobility, self-care, usual activities, pain/discomfort and anxiety/depression). Each dimension has five answer options that define different levels of severity. The EQ VAS records respondent’s self-rated health on a 20-mm vertical, visual analogue scale, ranging from 0 (worst imaginable health state) to 100 (best imaginable health state).

The HADS [22, 23] is a 14-item measure that evaluates psychological status. Seven items evaluate depression (the HADS-D subscale) and seven evaluate anxiety (the HADS-A subscale). A subscale score of 0 to 7 indicates the absence of anxiety or depression; 8 to10 a possible case of anxiety or depression; and 11 or higher a probable case of anxiety or depression.2.Outcomes:- Objective outcomes: Second primary malignancies, complications, recurrence (local, regional, or remote), and death.- Patient-reported outcomes: Changes in the EORTC-QLQ-C30, EORTC-QLQ-BR23, HADS and EQ-5D-5 L scores between the time of inclusion in the study and the follow-up, initially at 2 years and then at 5 years.

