### Complications

A checklist (yes/no) is used for complications throughout the course of the follow-up period (intra-surgical, during hospital admission, and up to 2 and 5 years after the intervention, including complications related to reconstructive surgery). When there is no information on complications in the medical record, it will be assumed that none occurred.

Surgical severity: We record the use of the following surgical techniques (ranked from least to most complex): conservative surgery (tumorectomy, quadrantectomy, and segmentectomy), simple mastectomy, radical mastectomy, modified radical mastectomy, skin-sparing mastectomy, nipple-sparing mastectomy, areola-sparing mastectomy, breast reconstruction and contralateral prophylactic mastectomy.

pTNM: Staging is performed following the American Joint Committee on Cancer [27, 28], being pTNM considered except for cases who received neoadyuvant therapy (cTNM).When there are no pTNM staging data, the analogous cTNM will be used, otherwise, missing value will be recorded. In cases of bilateral cancer, we will consider the final stage as a peak between right and left breast. In the cases of Tx, Nx or Mx, we will consider the disease to be T0, N0 or M0. If cM is missing, then cM will be considered to be 0.

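### The tumour definitions overlap with no order of precedence, so a later tumour in the opposite breast is not assigned to recurrence, second primary or metastatic disease

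*Protocol article*

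**What the plan says.** The section on missing data assumptions and recoding of variables gives the tumour definitions.

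- **Synchronous bilateral cancer:** bilateral tumours with different pathological diagnoses, found at diagnosis or within the next 6 months.
- **Metachronous bilateral cancer:** "two breast tumors that occur in contralateral breasts at two different time points (more than 6 months of difference) are categorized as metachronous bilateral breast" (last word omitted). This clause has no histology condition of its own.
- **Bilateral metastatic cancer:** "two breast tumors with the same pathological diagnosis are considered bilateral metastatic breast cancer". This clause has no time condition.
- **Recurrence:** "breast cancer that has come back during follow-up after a period in which cancer had not been detected", and, on site, "The cancer may come back in the same or opposite breast or chest wall".
- **Metastasis:** "disease that has spread to distant sites of the body, such as the liver, lungs, bone, brain, and/or other tissues or organs". The opposite breast is not named, but the list is open.

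The objective outcomes in the Variables section are "Second primary malignancies, complications, recurrence (local, regional, or remote), and death", so second primaries and recurrences are separate outcomes. The pTNM paragraph under Complications adds a staging rule: "In cases of bilateral cancer, we will consider the final stage as a peak between right and left breast".

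**The concern.** Relapse is the event on which the sample size calculation rests, and it is one of the outcomes for which a prediction rule is to be built and validated (Table 1; Statistical analysis). If the written rules allow the same contralateral tumour to be called a recurrence, a metachronous second cancer or metastatic disease, the event count depends on which rule the coder applies first. The event set could then mix returning disease with new primaries, whose predictors may differ. Hospital and regional variability is itself a study objective, so inconsistent coding could also pass for a real difference between centres.

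The same problem arises at baseline. A pair of tumours with matching diagnoses falls outside the synchronous definition and inside the metastatic one, yet the staging rule takes the higher of the two sides, which need not be a metastatic stage. Stage is an obvious candidate predictor.

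**Working it through.** **Applying the definitions.** Each row is a tumour in the opposite breast, set against every rule as written.

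| Time after the first tumour | Pathological diagnosis | Rules met |
|---|---|---|
| Up to 6 months | Different | Synchronous |
| Up to 6 months | Same | Bilateral metastatic; staged by the higher side under the pTNM rule |
| More than 6 months | Different | Metachronous; recurrence by site, if read as the cancer coming back |
| More than 6 months | Same | Metachronous; bilateral metastatic; recurrence, if read as the cancer coming back |

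Only the first row has a single, unqualified answer. In the last two rows nothing says whether the tumour counts as a recurrence or as a second primary malignancy.

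**The plan's own event figures** (Sample size calculation).

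- Planning: 100 events / 0.07 = 1429 women. The 1456 in Table 2 would give 1456 x 0.07 = 101.9 events.
- Observed so far: 1456 x 0.04 = 58.2 relapses. At 10 events per predictor, 58.2 / 10 = 5.8, which matches the stated limit of six.
- The 60/40 split leaves 0.6 x 58.2 = 34.9 events for derivation and 0.4 x 58.2 = 23.3 for validation. One miscoded derivation event is 1 / 34.9 = 2.9% of that set.

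**How many women could be affected.** The article gives no count or share of contralateral tumours, so this is an assumption range. Take an incidence of 0.2%, 0.4% or 0.6% a year. Count only months 6 to 24 (1.5 years), because the overlap between metachronous cancer and recurrence begins after month 6.

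| Assumed incidence per year | Tumours = 1456 x 1.5 x incidence | Share of 58.2 relapses | Relapses left if all are removed | Predictors at 10 events each |
|---|---|---|---|---|
| 0.2% | 4.4 | 7.5% | 53.9 | 5.4 |
| 0.4% | 8.7 | 15.0% | 49.5 | 5.0 |
| 0.6% | 13.1 | 22.5% | 45.1 | 4.5 |

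The share column is an upper bound for each assumed incidence: it supposes that every such tumour was counted as a relapse, which the article does not say.

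**Baseline staging.** Table 3 shows 18 + 11 = 29 women in stage IV. If some same-diagnosis pairs were moved into or out of that group, a few records would alter it visibly. The article does not say how many such pairs there are.

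**The case against.** The strongest defence is that the bilateral definitions can be read coherently. The sentence opens with tumours of different pathological diagnoses and moves on to the metachronous case. If the word for different carries through, three exclusive classes result: different and early is synchronous, different and late is metachronous, same is metastatic. Recurrence requires cancer that has come back, which can be read as excluding a new primary. An opposite-breast recurrence would then be same-diagnosis disease, recorded as metastatic recurrence. Reviewers also have a handbook, training and monthly data-quality checks, and the handbook is not shown.

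Part of this stands. The fault is overlap and ambiguity, and the text does not force a flat contradiction. But the grammar does not impose the coherent reading either, because the metachronous clause carries no histology condition. The reading also leaves the staging rule unreconciled. And the complaint is not about missing detail: these are the definitions the article chose to state.

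A reader might infer several stronger things that the document does not support.

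- **That a sizeable share of relapses cannot be classified.** No contralateral count is given. Relapses in the same breast, chest wall, regional nodes or distant sites are untouched.
- **That 10-30% of the endpoint is at stake.** That comes from counting the full 2 years (1456 x 2 x 0.002 to 0.006 = 5.8 to 17.5 women), which includes the first 6 months, when the metachronous rule does not apply.
- **That same-diagnosis pairs are coded as stage IV, or matched on a broad histological type alone.** The article does not say how the metastatic label enters TNM. It speaks of pathological diagnosis, and it collects differentiation, receptors and other markers besides type.
- **That hospitals have in fact coded differently.** This is possible but not shown. The labels may be applied at the recoding stage.
- **That contralateral tumours must be taken out of relapse.** Whether they belong there is partly a design choice; what is needed is that the choice be stated.

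**Conclusion.** The concern holds as a defect of definition. The written rules are not mutually exclusive, give no precedence between timing and histology, and do not separate recurrence from second primary for a contralateral tumour. The metastatic label for a same-diagnosis pair and the higher-side staging rule must be reconciled. This conclusion rests on the text alone and does not depend on any incidence.

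The size is unknown. Under the assumed 0.2-0.6% a year it is about 4 to 13 women against about 58 relapses, at most about 8-23% if all were counted as relapse. The 58 is itself approximate, since a rate rounded to 4% covers about 51 to 66 events (3.5% to 4.5% of 1456). Even the low end matters somewhat, because the plan already concedes that its events support no more than six predictors. It is worth settling before the relapse model is fitted.

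**What to change.** 1. Rewrite the bilateral, recurrence and metastasis definitions as mutually exclusive categories, with one stated order of precedence between timing and pathological diagnosis.
2. State which contralateral tumours count as relapse and which as second primary malignancy, so that the definitions agree with the outcome list in the Variables section.
3. Reconcile the same-diagnosis metastatic rule with the higher-side staging rule under Complications. Until that is done, a matching pathological diagnosis alone should not define metastatic disease.
4. Recode the affected records centrally, from the laterality, dates and pathology that the Variables section lists.
5. Report the number of contralateral tumours, and fit the relapse model with them counted as relapse and not counted, as a sensitivity analysis.

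The cost is a change of wording in the protocol and handbook and the recoding of what is probably a small number of records. The relapse count may fall slightly. If every contralateral tumour were removed under the assumptions above, about 45 to 54 events would remain, or 4.5 to 5.4 predictors at 10 events each.
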